### Study arms

Forty-one schools were randomized to one of the three conditions; school-led FRIENDS, health-led FRIENDS or treatment as usual (control). One school in the control arm withdrew after randomization.

### School-led friends

Each participating school will be asked to identify school staff (class teachers, special educational needs coordinators and/or teaching assistants) to deliver FRIENDS. These staff members will attend a two-day training event to familiarize them with the nature, extent and presentation of anxiety and depression in children and the CBT model. They will work through each of the FRIENDS sessions and have opportunities to practice the exercises and familiarize themselves with the materials and key learning points.

At each session the school staff will be assisted by two health professionals external to the school, to ensure that at least three adults are present in the class during the session delivery. The health professionals will not be responsible for leading the session but for supporting the school leader. During delivery of the program, biweekly supervision groups will be established to review session aims and content and address any problems with implementation.

### Health-led friends

This condition will be delivered by health professionals (Band 6, for example, school nurses, psychology assistants) external to the school (with the class teacher providing required assistance). These are not mental health specialists but health professionals with a lower level of training or expertise. They will receive the same initial training as specified above and will attend a biweekly supervision group.

### Treatment as usual

In this group, children will participate in the usual PSHE sessions provided by the school. These sessions will be planned and led by the class teacher.

In order to more specifically define Personal Social and Health Education (PSHE) within each school the head teacher, school PSHE coordinator and/or the year 5 class teacher will participate in a semi-structured interview. This interview will be undertaken at the end of the school term and will assess whether the school is following the national curriculum, what additional interventions might be running in the school and their content. The interview will determine the PSHE topics covered by the 9- and 10-year-old children during the study period, the way they are addressed (dedicated sessions, integration, circle time, etcetera), the length of time devoted to the PSHE curriculum and the number of adults (for example, teachers, assistants, volunteers, trainees) in the classroom.

### Outcome measures

All child outcome data are collected by self-completed questionnaires administered by researchers blind to the child’s trial allocation. Questionnaires are completed at school in classes at baseline, at 6 months and at 12 months.

### Primary outcome measures

The primary outcome measure notes changes in the level of symptoms on the Revised Child Anxiety and Depression Scale (RCADS)
[23]. This is a recent modification of the Spence Children’s Anxiety Scale
[24], which was revised to correspond more closely to DSM-IV criteria for anxiety and depression
[25]. The 30-item scale (RCADS-30) assesses anxiety in the areas of social phobia, separation anxiety, obsessive compulsive disorder, panic disorder and generalized anxiety disorder and also assesses major depressive disorder. The RCADS-30 has good internal consistency, test-re-test stability and good convergent and divergent validity
[26,27].

### Secondary outcomes

Children will complete the Rosenberg Self-Esteem Scale to assess changes in self-worth and acceptance
[28]. The Penn State Worry Questionnaire for Children
[29] assesses the tendency of children to engage in excessive, generalized and uncontrolled worry. The degree to which children have bullied others or have been the victim of bullying, satisfaction with six aspects of everyday life (school, appearance, family, home, friendships and health), and overall life satisfaction (subjective well-being) will be assessed.

Parents will be asked to complete the Strength and Difficulties Questionnaire (SDQ), a brief, widely used behavioral screening questionnaire that assesses emotional symptoms, conduct problems, hyperactivity and/or inattention, peer relationship problems, and prosocial behavior
[30,31]. The Parent completed Revised Child Anxiety and Depression Scale (RCADS-30-P) is a 30-item parent version of the primary outcome measure completed by children. The RCADS-30-P has high internal consistency, test-re-test reliability and good convergent and divergent validity
[32].

Class teachers will be asked to complete the impact rating of the Strengths and Difficulties Questionnaire (SDQ) for all children in their class. This assesses the teacher perception of whether a child has a problem, and if so, enquires about chronicity, distress, social impairment and burden.

### Outcomes for the economic evaluation

In order to assess cost-utility, all children will complete the Child Health Utility-9D (CHU-9D) at baseline and at 6 and 12 months
[33]. The CHU-9D, a validated measure of pediatric health-related quality of life, is short (nine items) and has been specifically developed for use with children aged 7 to 11 years. The use of the CHU-9D will allow us to assess how improvements in mental health (anxiety and depression) translate into changes in overall health-related quality of life.

For collecting health, social care and educational resource use data, structured interviews will be conducted with a sample of carers/parents for each of 300 children, with approximately 100 children from each of the three conditions. All parents will be invited to participate and they will be offered £20 to cover the cost of their time. They will complete the Client Receipt of Services Questionnaire, a structured interview that assesses their child’s use of social, health and educational services over the past 6 months
[34]. In addition, a screen of parental health and mental health, assessment of life events and a survey of child leisure and sport activities will be undertaken.

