### School recruitment

A list of 268 primary schools in Bath and North East Somerset, and in Swindon and Wiltshire was compiled from Local Authority information. Project information sheets were sent to the head teachers and meetings arranged with the 45 (17%) schools who expressed interest. Four schools did not return signed letters confirming participation before randomization and were therefore excluded. A total of 41 schools were randomized with one school withdrawing after randomization. The cohort therefore consisted of 40 schools (1,448 eligible children).

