### Power calculation

The study was powered to detect a difference between FRIENDS (Health- and School-led) and usual PSHE. Based on an intra-cluster correlation coefficient (ICC) of 0.02, 28 pupils per class, 90% consent and 80% retention, effect sizes in the range of 0.28 to 0.30 SDs are detectable with 80% power and 5% two-sided alpha with 45 to 54 schools (that is, 1,134 to 1,360 consenting pupils). A standardized treatment effect size of 0.3 is equivalent to an estimated difference on the RCADS-30 of 3.6 points based on an SD of 12.

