### Economic evaluation

The analysis of the cost data, the CHU-9D data and cost-effectiveness analysis will be conducted according to current best practice methods for conducting economic evaluation alongside trials,
[37,38] and specifically alongside cluster-randomized controlled trials
[39]. Incremental costs, incremental effects, and where relevant incremental cost-effectiveness ratios (ICERs) will be estimated, comparing the three conditions. The incremental cost per unit quality-adjusted life year (QALY) increase will be estimated. Both unadjusted analyses and adjusted analyses will be carried out, adjusting for site, mode of delivery, number of students and number of classes.

Random effects bivariate linear regression models will be fitted to model cost and effectiveness (QALY) simultaneously, allowing for correlation within clusters and correlation between cost and effectiveness score within participants
[40]. From these models we will estimate: the mean difference in costs of the three conditions and corresponding standard error; the mean difference in effect and corresponding standard error; and, indirectly via the variance-covariance matrix of the regression coefficients, the correlation between the mean cost difference and the mean effect difference. Where the interventions are estimated to have both higher costs and greater effectiveness than control, we will use Fieller’s method to obtain a parametric estimate of the 95% confidence interval for the ICER and to construct the cost-effectiveness acceptability curve (CEAC). Both parametric and non-parametric bootstrap estimates of the confidence interval for the ICERs will be estimated.

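### Service-use costs will be observed for only about a fifth of the cohort, recruited by open paid invitation, and the listed economic adjustment set has no child-level variable to correct for who accepts

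*Protocol article*

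**What the plan says.** The section *Outcomes for the economic evaluation* sets up two data streams of very different coverage. For utilities, "all children will complete the Child Health Utility-9D (CHU-9D) at baseline and at 6 and 12 months". For resource use, "structured interviews will be conducted with a sample of carers/parents for each of 300 children, with approximately 100 children from each of the three conditions". The instrument is "a structured interview that assesses their child’s use of social, health and educational services over the past 6 months". On how families enter the interview group, the article gives one rule: "All parents will be invited to participate and they will be offered £20 to cover the cost of their time". It does not say how the 300 are chosen if more parents accept, or when the invitation is sent.

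The section *Economic evaluation* then brings the two streams together: "Random effects bivariate linear regression models will be fitted to model cost and effectiveness (QALY) simultaneously". The model is to account for clustering and for the association between a child's own cost and QALY. The adjusted analysis lists trial site, delivery mode, pupil numbers and class numbers as covariates. It names no characteristic of the child or family. It does not say whether the model is fitted to the interviewed children or to everyone.

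**The concern.** A numerical target combined with an open invitation makes the cost sample whoever agrees. Aiming for about 100 per arm equalises the counts. It does not equalise the kind of family that agrees, and it can hide different acceptance rates between arms.

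There is a plausible route to differential acceptance. All schools had been recruited and randomized by September 2011, the month in which baseline assessment and delivery began (*Study status*), so parents may know their school's allocation. FRIENDS parents are also offered a session and receive summary sheets (*Intervention*), and nothing equivalent is described for control parents (*Treatment as usual*).

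At stake is the cost side of the incremental cost-effectiveness ratio and the acceptability curve. The effectiveness side describes whole year groups. The service-use side would rest on consenting families, and no listed covariate could adjust for how they differ from the others.

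**Working it through.** **Inputs**
- Interview target: 300, about 100 in each of three conditions (*Outcomes for the economic evaluation*).
- Cohort: 1,448 eligible children in 40 schools (*School recruitment*).
- Planning rates: "28 pupils per class, 90% consent and 80% retention" (*Power calculation*).
- ICC: 0.02 (*Power calculation*), set for the trial's main comparison. Using it for CHU-9D is an assumption.

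**Step 1. Reproduce the plan's figures.** 3 × 100 = 300. The planned consenting numbers also reproduce: 45 × 28 × 0.9 = 1,134 and 54 × 28 × 0.9 = 1,360.8. This confirms how the 90% consent rate is applied.

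**Step 2. Share of children with service-use costs**

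| Denominator | n | 300/n | No cost data |
|---|---|---|---|
| Eligible | 1,448 | 20.7% | 79.3% |
| 90% consent | 1,448 × 0.9 = 1,303 | 23.0% | 77.0% |
| 90% consent, 80% retained | 1,303 × 0.8 ≈ 1,043 | 28.8% | 71.2% |
| Planned, lower | 1,134 | 26.5% | 73.5% |
| Planned, upper | 1,360 | 22.1% | 77.9% |

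Costs are unobserved for roughly 71% to 79% of children on every denominator.

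**Step 3. When this biases the incremental cost.** Let f be the interviewed share and D the mean cost of participants minus that of others, in SD units, within an arm. The interviewed mean is off by (1 − f) × D. With f = 0.207 and D assumed to lie between 0.1 and 0.3 (not in the document), the error in an arm's mean is 0.793 × 0.1 = 0.08 to 0.793 × 0.3 = 0.24 SD.

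With equal f in each arm, the error in the difference between arms is (1 − f) × (D₁ − D₀). If D is the same in both arms, it cancels. It remains if acceptance selects different families in the two arms, or if the intervention's effect on cost differs between participants and others. As an illustration, D₁ = 0.3 against D₀ = 0.1 gives 0.793 × 0.2 = 0.16 SD. The document supplies no value for D in any arm.

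**Step 4. Precision if QALYs were also confined to the 300.** Assume 40 equal schools and ICC 0.02.
- All consenting: 1,303/40 = 32.6 per school; design effect 1 + 31.6 × 0.02 = 1.63.
- Interviewed: 300/40 = 7.5 per school; design effect 1 + 6.5 × 0.02 = 1.13.
- Standard error ratio: √[(1.13/300) ÷ (1.63/1,303)] = 1.73.
- Against 1,043 retained children: 26.1 per school, design effect 1.50, ratio 1.62.
- Ignoring clustering gives √(1,303/300) = 2.08, which overstates the loss in this cluster design.

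**Step 5. When random ordering changes the sample.** It does so only if more than 300 parents would accept, that is, if acceptance exceeds 300/1,448 = 20.7% of eligible families or 300/1,303 = 23.0% of consenting ones. Below that the list is exhausted and the sample is the same as under open invitation. The document gives no expected acceptance rate.

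**The case against.** The case against is substantial, and several parts of it stand.

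- **The joint model.** A reader might infer that modelling cost and QALY together requires both values, so that children without an interview are dropped. The article does not say this. A likelihood-based bivariate model can keep children who have QALYs but no cost, under a missing-at-random assumption. Only the correlation within participants needs children with both values.
- **Timing.** A reader might also infer that parents are invited after FRIENDS families have had their extra contact. The invitation date is not given, and an invitation at baseline could precede that contact.
- **Scope of the costs.** It would be too strong to say that all costs in the ICER come from these families. The interview covers services used. The cost of delivering FRIENDS does not come from it.
- **Bias is not shown.** A sample with a different mean cost does not by itself distort the difference between arms (Step 3).
- **Random ordering is not a cure.** Any consent-based interview is open to refusal, and the payment might widen participation.
- **Detail left elsewhere.** Handling of missing costs is commonly left to a fuller protocol or analysis plan. The article commits to current best practice for economic evaluation alongside cluster trials, and *Statistical analysis* plans imputation and a comparison of completers with non-completers. Costs are neither named nor excluded there.

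The last point limits the criticism but does not remove it. The open invitation and the adjustment list are choices the article states. A later analysis plan could improve the handling of missing costs, but it could not turn the interviewed families into a probability sample.

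**Conclusion.** The concern holds in a limited form. Service-use costs will be observed for about 300 children, 21% of those eligible or 23% at 90% consent, whose parents accept an open paid invitation. CHU-9D is sought from everyone. The incremental cost and ICER could be biased if acceptance differs by arm or if the effect on cost differs between participants and others. Neither condition is established, and the document does not allow size or direction to be determined. The listed adjustment variables contain nothing at child level that could correct such selection.

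If QALYs were restricted to the 300, their standard error would be about 1.7 times that from all consenting children, assuming ICC 0.02 and 40 equal schools. The document does not say they will be restricted, so this is a conditional cost and not a consequence of the plan as written. The point concerns the economic evaluation and leaves the primary outcome untouched.

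**What to change.** **Sampling.** In *Outcomes for the economic evaluation*, replace the open invitation by a random order within each school, stratified by baseline RCADS, and invite parents in that order until about 100 per arm are reached. State that this limits selection of early responders but not refusal. Record invitations and refusals, report acceptance by arm, and compare baseline RCADS and CHU-9D between interviewed and non-interviewed children within each arm.

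**Analysis.** In *Economic evaluation*, state that QALYs are estimated in all children with CHU-9D data. Add baseline CHU-9D and baseline RCADS to the bivariate model, or to multilevel imputation or inverse-probability weighting of costs. Present the interviewed-only result as a sensitivity analysis. If interview recruitment is already complete, the comparison of interviewed with other children and these analysis steps can still be done, because both baseline measures are collected in any case.

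**Cost.** Interview recruitment would be somewhat slower and some analysis would be added. The result would still rely on a missing-at-random assumption with most costs unobserved, and this should be stated alongside the ICER.

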### Power calculation

The study was powered to detect a difference between FRIENDS (Health- and School-led) and usual PSHE. Based on an intra-cluster correlation coefficient (ICC) of 0.02, 28 pupils per class, 90% consent and 80% retention, effect sizes in the range of 0.28 to 0.30 SDs are detectable with 80% power and 5% two-sided alpha with 45 to 54 schools (that is, 1,134 to 1,360 consenting pupils). A standardized treatment effect size of 0.3 is equivalent to an estimated difference on the RCADS-30 of 3.6 points based on an SD of 12.

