### Statistical analysis

Data analysis will be undertaken blinded to allocation. Analysis and presentation of data will be in accordance with Consolidated Standards of Reporting Trials (CONSORT) guidelines and in particular the extension to cluster randomized trials
[35]. The primary comparative analyses will be conducted on an intention-to-treat (ITT) basis with due emphasis placed on confidence intervals for the between-arm comparisons. Descriptive student- and class-level statistics will be used to ascertain any marked imbalance between the arms at baseline.

The primary analysis will employ a mixed effect linear regression model to compare the active CBT interventions (health- and school-led) versus treatment, adjusting as usual for stratification variables and baseline score, and taking appropriate account of the hierarchical nature of the data (repeated measures, children, classes and schools). Sensitivity analyses making different assumptions will be conducted to investigate the potential effects of missing data.

The extent of missing data will be reported and baseline factors will be compared for completers and non-completers to assess the extent of any bias that may result. Analysis will be undertaken using intention to treat (ITT). The potential for bias, dependent on the extent of missing data, will be assessed. Using the framework specified by White *et al.* an appropriate approach will be used to impute missing values in both outcome and descriptor variables
[36]. A further complete case analysis may also be undertaken and compared to the intention to treat results.

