Secondary analyses will include: 1) repeating the primary analysis adjusting for any variables exhibiting marked imbalance at baseline to examine whether this influences the findings; 2) comparison of children who score high (that is, top 10% of total RCADS scores in each trial arm) and low on anxiety and mood at baseline (that is, remaining 90%) to examine who most benefits from these interventions; 3) similar analyses for other secondary outcomes (using appropriate multi-level models and adjusting *P* values for multiple testing); 4) investigation of process measures such as number of sessions attended; and 5) investigation of possible treatment moderators (for example, gender) and mediators (for example, school pedagogic orientation). Finally, although the study is not sufficiently powered to detect a difference between the two FRIENDS arms (school- and health-led) an exploratory analysis will be undertaken.

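### The stated detectable effect of 0.28 to 0.30 SD does not follow from the stated inputs for pooled FRIENDS versus PSHE; those inputs give about 0.21 to 0.24 SD

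*Protocol article*

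**What the plan says.** The Power calculation section names the contrast: "The study was powered to detect a difference between FRIENDS (Health- and School-led) and usual PSHE". It gives the inputs: "Based on an intra-cluster correlation coefficient (ICC) of 0.02, 28 pupils per class, 90% consent and 80% retention". From these it concludes that "effect sizes in the range of 0.28 to 0.30 SDs are detectable with 80% power and 5% two-sided alpha with 45 to 54 schools". It adds that 45 to 54 schools mean 1,134 to 1,360 consenting pupils, and that 0.3 SD is 3.6 points on the RCADS-30 with an SD of 12.

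The Statistical analysis section makes the same pooled contrast primary: the model is to "compare the active CBT interventions (health- and school-led) versus treatment" as usual. It also says that "the study is not sufficiently powered to detect a difference between the two FRIENDS arms (school- and health-led"), so that comparison is exploratory.

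The School recruitment section reports what was achieved: "The cohort therefore consisted of 40 schools (1,448 eligible children"). The Study arms section says that the school that withdrew was in the control arm. No allocation ratio is stated.

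**The concern.** Everything needed to check the detectable effect is printed except the allocation ratio. With equal arms, pooling two of them against one gives a noticeably smaller detectable effect than the one stated. Either the range is wrong for the contrast named, or the contrast and alpha attached to the range are wrong.

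This sentence tells readers how to interpret a null result. As printed, about 3.4 to 3.6 RCADS points looks like the limit of what the pooled comparison can detect at 80% power. If the inputs hold, the limit is roughly 2.5 to 2.8 points. A reader also cannot tell whether the range was meant for the pooled contrast or for each FRIENDS arm separately.

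**Working it through.** **Inputs.** From the Power calculation section: ICC 0.02; 28 pupils per class; 90% consent; 80% retention; two-sided alpha 5%; power 80%; SD 12; 45 to 54 schools. Assumed: equal allocation to three arms, hence 2:1 for pooled FRIENDS versus PSHE.

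**Figures that reproduce.** 45 × 28 × 0.9 = 1,134; 54 × 28 × 0.9 = 1,360.8; 0.3 × 12 = 3.6. The pupil totals show that the plan counts one class of 28 per school.

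**Cluster size and design effect.** Analysed pupils per school: m = 28 × 0.9 × 0.8 = 20.16. DE = 1 + (m − 1) × ICC = 1 + 19.16 × 0.02 = 1.383.

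**Pooled contrast.** SE = √[DE × (1/n₁ + 1/n₂)]; detectable effect = (1.960 + 0.842) × SE = 2.802 × SE.

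- 45 schools (30 v 15): n = 604.8 v 302.4; SE = 0.0828; detectable effect 0.232 SD (0.237 with t quantiles on 43 df).
- 54 schools (36 v 18): n = 725.8 v 362.9; SE = 0.0756; detectable effect 0.212 SD (0.216 with t on 52 df).

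In points: 0.212 × 12 = 2.5 and 0.232 × 12 = 2.8. The printed range is 0.28 × 12 = 3.4 to 0.30 × 12 = 3.6.

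**Power for the stated effects, pooled.** For 0.30 SD: 95% with 45 schools (94% with t) and 98% with 54 (97% with t). For 0.28 SD: 92% and 96% (91% and 95% with t). By the normal formula, 80% power needs about 45 × (0.232/0.30)² = 27 schools for 0.30 SD and 45 × (0.232/0.28)² = 31 for 0.28 SD.

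**What would produce 0.28 to 0.30?**

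| Variant, m = 20.16 | 45 schools | 54 schools |
|---|---|---|
| Pooled 2:1, 5% alpha, 80% power | 0.232 (t 0.237) | 0.212 (t 0.216) |
| Same, cluster-size CV 0.8 (assumed) | 0.253 | 0.231 |
| One arm v PSHE, 5% alpha, 80% power | 0.268 (t 0.278) | 0.245 (t 0.252) |
| One arm v PSHE, 2.5% alpha, 80% power | 0.295 (t 0.309) | 0.269 (t 0.280) |
| One arm v PSHE, 5% alpha, 90% power | 0.310 | 0.283 |

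For the pooled contrast to give the range at 5% alpha and 80% power, the ICC would have to be about 0.07 (0.068 for 0.30 SD with 45 schools; 0.074 for 0.28 SD with 54), or the control arm would have to hold only about 7 to 8 schools. At the stated 80% power, the simple variant that comes close at both ends is one arm versus PSHE at 2.5% alpha. The 90% power row is also near, but it departs from the stated power as well as the stated contrast.

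**Recruited cohort.** 1,448/40 = 36.2 eligible per school; m = 36.2 × 0.72 = 26.06; DE = 1 + 25.06 × 0.02 = 1.501. The split by arm is not given. If it is 27 v 13, SE = 0.0810 and the pooled detectable effect is 0.227 SD (0.233 with t), or 0.237 (0.243 with t) if the cluster-size CV is 0.5. With equal cluster sizes, 12 control schools give 0.232 and 14 give 0.223. At 27 v 13 with equal clusters, power for 0.30 SD is about 96% (95% with t).

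**The case against.** The strongest reply is that the range may come from a legitimate calculation that lost its label. Naming FRIENDS with both delivery modes in brackets could mean each arm against PSHE, and a split alpha would then be natural. With t quantiles that gives 0.309 and 0.280, close to what is printed. The full protocol behind this condensed article may say so. Nor does the remark about low power between the two FRIENDS arms exclude it, since two active arms would be expected to differ by less than 0.3 SD. This has weight: it makes labelling the calculation as valid a remedy as replacing the range. It does not rescue the sentence as printed, which pairs the range with an undivided 5% alpha, in an article whose primary analysis pools the arms. The split-alpha origin remains an inference.

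The reply is also right on several stronger readings that a reader might draw.

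- *That 40 schools against 45 to 54 is an error, or leaves the trial underpowered.* The calculation is a priori and recruitment is openly reported. Expected consenters, 1,448 × 0.9 = 1,303, lie inside the planned 1,134 to 1,360. On the planned assumptions, pooled power for 0.28 to 0.30 SD stays above 90% for 12 to 14 control schools of equal size.
- *That 36.2 pupils contradicts 28.* The first is per school and the second per class. The Randomization section shows that schools varied in number of classes.
- *That the smaller effect is paired with fewer schools.* Two ranges are each listed in ascending order, and nothing pairs their ends.

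**Conclusion.** The point holds as an arithmetic inconsistency in one sentence. For the contrast, alpha and power stated, the inputs give about 0.21 to 0.23 SD (0.22 to 0.24 with t quantiles) instead of 0.28 to 0.30, a difference of roughly 0.8 RCADS points at each end. The result rests on equal three-arm allocation, but no plausible departure closes the gap: two equal halves would lower the detectable effect further, and only a very small control arm would raise it enough.

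The error is conservative. It understates what the pooled comparison can detect and leaves the design, primary contrast and analysis untouched. It is a reporting correction. The figures for the recruited cohort are indicative only, because the split by arm and the spread of school sizes are assumed.

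**What to change.** Amend the Power calculation section in one of two ways.

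1. Correct the range to about 0.21 to 0.24 SD (2.5 to 2.8 points, normal quantiles) for pooled FRIENDS versus PSHE with 45 to 54 schools, and state the allocation ratio.
2. Keep 0.28 to 0.30, state the contrast, allocation and alpha that produce it, and give the pooled figure beside it.

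Either way, keep the a priori calculation as the record of what was planned. Add one line for the recruited cohort (40 schools, 1,448 eligible children), computed with the actual number of schools per arm. That figure is about 0.23 to 0.24 SD if the split is 27 v 13 and ICC, consent and retention are as planned, the upper end allowing for unequal school sizes.

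The cost is rewording one paragraph. No extra schools, pupils or data are needed.
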